### Protocol amendment

The principal investigator will be accountable for any protocol amendments and render the final determination. Should any critical protocol modifications arise (e.g., changes to eligibility criteria, outcomes, analyses), the principal investigator will communicate and secure approval from the local Medical Ethics Committee before implementation. Any revised protocol will be updated on the ClinicalTrials.gov registry website.

### Safety considerations

The apparatus employed in this study is hydrogen–oxygen generator with nebulizer (AMS-H-03, Shanghai Asclepius Meditech Co., Ltd. China) (Fig. 2). A comprehensive review has furnished in-depth insights into the device’s underlying principles, safety features, and its method of application within the trial [25]. In addition to the device’s specialized design, stringent safety measures will be implemented, including the conduction of the study within a well-ventilated environment and the utilization of an ambient hydrogen concentration monitor to ensure that the hydrogen concentration in the surroundings remains below 4%.

**Fig. 2 Fig2:**
[figure not shown]
A schematic diagram of the hydrogen/oxygen generator (model AMS-H-03). Courtesy of Shanghai Asclepius Meditec Co., Ltd. (Shanghai, China)

### Sample size estimates

PASS (Version 15.0) software was utilized for sample size determination. The primary study outcomes encompass the incidence of in-hospital DCI and CVS, both exhibiting nearly equivalent prevalence rates. Drawing from our current retrospective and prospective data, we anticipate a prevalence of 23% in the experimental group and 45% in the control group. With a significance level (*α*) of 0.05 and a desired statistical power of 90%, the necessary sample size per study arm to discern this difference is calculated to be 103 patients.

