**Methods:**

Early *H*ydrogen–*O*xygen Gas *M*ixture *I*nhalation in Patients with Aneurysmal Subarachnoid Hemorrhage (HOMA), a single-center, prospective, open-labeled, randomized controlled clinical trial, endeavors to evaluate the efficacy and safety of hydrogen–oxygen gas mixture inhalation therapy in aSAH patients. A cohort of 206 patients will be randomized to either hydrogen–oxygen gas mixture inhalation group (8 h per day, 3 L/min, hydrogen concentration of 67%, oxygen concentration of 33%) or oxygen inhalation group (8 h per day, 3 L/min, oxygen concentration of 33%) within 72 h after aSAH and treated for 7 days in the ICU ward. The primary outcomes are the incidence of DCI and CVS during hospitalization.

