**Discussion:**

The HOMA aims to evaluate the effectiveness of hydrogen–oxygen gas mixture inhalation therapy in preventing DCI or CVS and improving outcomes in aSAH patients. Notably, this is the first large-scale trial of hydrogen therapy in aSAH patients. Given that the Chinese population represents a significant portion of the global population and the increasing incidence of stroke due to aging, optimizing patient care is vital. Given the current challenges in aSAH patient outcomes, initiating more prospective clinical trials is essential. Recent research has shown hydrogen’s therapeutic potential, aligning with EBI in aSAH, driving our exploration of hydrogen therapy’s mechanisms in post-aneurysm rupture damage.

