### Statistical analysis

We will conduct data analysis in accordance with the intention-to-treat principle. Continuous variables will be presented as mean ± standard deviation (SD) or median along with interquartile range (IQR). Categorical variables were summarized as frequency (percentage). Continuous variables will be assessed using either the independent Student’s *t*-test (assuming normal distribution) or the Mann–Whitney *U* test. Dichotomized variables will be compared utilizing the Pearson chi-square test or Fisher’s exact test. To mitigate preoperative confounding factors, a multiple regression analysis will be employed to compare outcomes between the two groups. The results will be reported as adjusted odds ratios (OR) accompanied by 95% confidence intervals (CI), with OR values below 1 indicating a treatment effect in favor of hydrogen–oxygen mixture therapy. Postoperative follow-up assessments at designated time intervals are imperative, and the absence of data should not be anticipated. Statistical significance will be defined as a threshold of *P* < 0.05.

Subgroups analysis will be performed, including subgroup by age, sex, WFNS, mFS, and treatment modality. Subgroup analyses are limited to the primary efficacy endpoint and safety endpoint only. Separate logistic models will be applied to each subgroup during subgroup analysis.

There will be no interim analyses in this trial.

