## Discussion

HOMA represents a single-center, prospective, open-label, and randomized controlled clinical trial, aimed at assessing the potential of hydrogen–oxygen gas mixture inhalation therapy in averting DCI or CVS while ameliorating outcomes in patients afflicted by aSAH. It is worth noting that this constitutes the first large-scale clinical trial of hydrogen therapy as applied to aSAH patients.

The Chinese population accounts for approximately one-fifth of the global population. With the advent of the aging demographic epoch, the incidence of stroke has been on a steady rise, posing a significant menace to public health. Consequently, the optimization of patient care has assumed paramount importance within the healthcare system.

Given the current impasse in substantially improving outcomes for aSAH patients, clinicians should be prompted to initiate additional prospective clinical trials. Recent years have witnessed the unequivocal validation of hydrogen has therapeutic potential in basic research [26, 27]. We posit that hydrogen’s therapeutic attributes closely align with the concept of EBI following aSAH. Therefore, we embarked on the utilization of hydrogen therapy in aSAH patients, with the aim of elucidating potential mechanisms underlying post-aneurysm rupture bodily damage.

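### Two primary outcomes (DCI and CVS) share one sample size calculation and an unadjusted 0.05 threshold, with no rule for which results make the trial positive

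*Protocol article*

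**What the plan says.** The abstract states "The primary outcomes are the incidence of DCI and CVS during hospitalization". The Primary outcomes section lists DCI and CVS as two items, each with its own diagnostic criteria, so they are not a composite.

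The Sample size estimates section covers both with one calculation. It states "The primary study outcomes encompass the incidence of in-hospital DCI and CVS, both exhibiting nearly equivalent prevalence rates", gives one pair of rates (23% experimental, 45% control) with a significance level "of 0.05 and a desired statistical power of 90"%, and arrives at 103 patients per arm.

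The Statistical analysis section has one sentence on error control: "Statistical significance will be defined as a threshold of" P < 0.05. It gives no alpha split, testing order or joint-success rule, and it rules out interim analyses. The same section speaks of one primary endpoint: "Subgroup analyses are limited to the primary efficacy endpoint and safety endpoint only".

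The discussion part of the abstract describes the aim as "preventing DCI or CVS and improving outcomes in aSAH patients", and the main Discussion as "averting DCI or CVS while ameliorating outcomes in patients afflicted by aSAH".

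**The concern.** With two primary outcomes, the meaning of 5% error and 90% power depends on which pattern of results counts as success. The article fixes the sample size and the threshold but not the pattern.

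- If a significant result on either outcome is enough, two tests at the full 0.05 give two chances of a false positive.
- If both must be significant, the error rate is safe, but the chance of winning on both is lower than the chance of winning on one.
- If one outcome is significant and the other is not, the article gives no way to say whether the trial succeeded.

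A split result is realistic. By the article's own definitions, DCI can be diagnosed with or without radiographic vasospasm, and CVS can be met on transcranial Doppler velocity alone. In an open-label, single-center trial, a success rule left open until the results are known allows the more favorable outcome to be emphasized.

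**Working it through.** **Inputs.** From Sample size estimates: p1 = 0.23, p2 = 0.45, alpha = 0.05, power 90%, n = 103 per arm. From Randomization: 1:1 allocation. From Statistical analysis: Pearson chi-square or Fisher's exact test, threshold 0.05, no interim analyses. **Assumed:** two-sided tests, because sidedness is not stated; the same rates for both outcomes, as the article implies; and a correlation ρ between the two test statistics from 0 to 0.9, because none is given.

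**1. The plan's own figure.** The mean rate is p̄ = 0.34. Then √(2p̄(1−p̄)) = √0.4488 = 0.6699 and √(p1(1−p1) + p2(1−p2)) = √0.4246 = 0.6516.

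n = (1.960 × 0.6699 + 1.2816 × 0.6516)² / 0.22² = 95.3, so 96 per arm, or 105 with continuity correction.

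Exact power at 103 per arm is 89.9% with Fisher's test and 92.2% with chi-square. So 103 is a sound size for **one** binary outcome tested alone at two-sided 0.05.

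**2. Power per outcome at 103 per arm** (pooled normal formula):

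Power = Φ[(0.22√103 − z × 0.6699) / 0.6516]

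- alpha 0.05: Φ[(2.2328 − 1.3130) / 0.6516] = Φ(1.41) = 92.1%
- alpha 0.025: Φ[(2.2328 − 1.5016) / 0.6516] = Φ(1.12) = 86.9%

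**3. If either outcome suffices, each at 0.05.** For independent tests the family-wise error is 1 − 0.95² = 9.75%. For correlated tests it is 1 − P(|Z1| < 1.96 and |Z2| < 1.96) under a bivariate normal.

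**4. If both outcomes are required, each at 0.05.** The family-wise error is at most 5%. Joint power is P(Z1 < q and Z2 < q) with q = Φ⁻¹(marginal power). For independent tests this is 0.921² = 84.8%, or 0.90² = 81.0% if each test has exactly the stated 90%.

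| Correlation | Error, either suffices | Joint power, 92.1% each | Joint power, 90% each |
|---|---|---|---|
| 0 | 9.75% | 84.8% | 81.0% |
| 0.5 | 9.07% | 86.5% | 83.2% |
| 0.7 | 8.35% | 87.7% | 84.7% |
| 0.9 | 7.04% | 89.5% | 86.9% |

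Error stays above 5% in the second column at every correlation tried, and power stays below 90% in the last two.

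**5. What restoring 90% would cost without a testing order.** A Bonferroni split at 0.025 needs 113 per arm (122 with continuity correction) for 90% power on each outcome. Requiring both needs 117 per arm (126 with correction) for 90% joint power if the tests are independent.

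**6. Holm at 103 per arm.** An outcome is claimed if its P is below 0.025, or if its P is below 0.05 and the other outcome's is below 0.025. If both effects are as assumed, per-outcome chi-square power is 91.4% at ρ = 0 and about 89% at ρ = 0.9. If only one effect is real it is about 87%: 0.869 + (0.921 − 0.869) × 0.025 = 0.870 for independent tests.

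**The case against.** The strongest reply is that this is a condensed article. A success rule and a multiplicity procedure commonly sit in the full protocol or statistical analysis plan, neither of which is shown. A fixed-sequence rule there would test both outcomes at 0.05 and be compatible with everything printed here. That stands to this extent: the article does not show that an inflated claim will be made, only that nothing in it prevents one.

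It does not dispose of the point. The article itself names two primary outcomes, sizes the trial on one test at the full 0.05 and prints one unadjusted threshold. A later Bonferroni split would leave about 87% power per outcome with chi-square, and a both-must-win rule 81–89% jointly. Neither delivers the 90% printed for the two outcomes. A fixed order would, but only for the outcome tested first, and the article does not say so.

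Two stronger readings are tempting and are not supported:

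- A reader might infer a contradiction because the outcomes are joined by *and* in the abstract's methods and by *or* in the discussion passages. Those passages are descriptive prose about the aim, and the Background uses both conjunctions interchangeably. They state no decision rule. The defect is the missing rule.
- A reader might infer that the trial has lost both its 5% error and its 90% power. The harms belong to mutually exclusive readings. Where error is inflated, the chance of winning on at least one outcome is about 95–99% (92.1% marginal power, both effects as assumed). Where joint power falls short, error is controlled.

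**Conclusion.** The point holds. As printed, the 5% error and the 90% power are jointly secured only for one outcome tested alone, and the trial has two. The excess is 2 to nearly 5 percentage points of family-wise error if either outcome suffices (7.0% to 9.75%). The shortfall in joint power if both are required is about 0.5 to 5 points from the 92.1% chi-square marginal, or 3 to 9 points if each test has exactly 90%. *Nearly double* the nominal error describes only the end of the range near independence. The article presents DCI and CVS as linked consequences of early brain injury, so some positive correlation is plausible, but it gives no value.

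These figures rest on two-sided tests, equal rates for both outcomes and a bivariate normal approximation. The figure of 103 per arm is not wrong in itself. The error lies in letting a single-outcome calculation stand for two primary outcomes without a success rule. The matter bears on the trial's main claim and cannot be credibly settled once results are known.

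**What to change.** Before any outcome data are analysed, state a fixed testing order in the Statistical analysis section. One example is DCI, which is listed first, at two-sided 0.05, then CVS at 0.05 only if DCI is significant. No part of the article ranks the two outcomes, so the order is the sponsor's choice. State in the Sample size estimates section that the 90% power refers to the first outcome, and that power to claim both is about 81–89% depending on the correlation and the test. Name the primary outcomes in the plural, or name the first one, where the subgroup sentence speaks of a single primary endpoint.

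If the sponsor wants either outcome to count, use Holm. State per-outcome chi-square power of about 87% if only one effect is real and about 89–91% if both are as assumed. The 87% should not be quoted as Holm's power in general.

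The cost is a wording amendment, with ethics approval and a registry update as the Protocol amendment section requires. The sample size stays at 206. The downside of a fixed order is that the second outcome cannot be claimed if the first fails. The downside of Holm is a slightly lower stated power per outcome.

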### Statistical analysis

We will conduct data analysis in accordance with the intention-to-treat principle. Continuous variables will be presented as mean ± standard deviation (SD) or median along with interquartile range (IQR). Categorical variables were summarized as frequency (percentage). Continuous variables will be assessed using either the independent Student’s *t*-test (assuming normal distribution) or the Mann–Whitney *U* test. Dichotomized variables will be compared utilizing the Pearson chi-square test or Fisher’s exact test. To mitigate preoperative confounding factors, a multiple regression analysis will be employed to compare outcomes between the two groups. The results will be reported as adjusted odds ratios (OR) accompanied by 95% confidence intervals (CI), with OR values below 1 indicating a treatment effect in favor of hydrogen–oxygen mixture therapy. Postoperative follow-up assessments at designated time intervals are imperative, and the absence of data should not be anticipated. Statistical significance will be defined as a threshold of *P* < 0.05.

Subgroups analysis will be performed, including subgroup by age, sex, WFNS, mFS, and treatment modality. Subgroup analyses are limited to the primary efficacy endpoint and safety endpoint only. Separate logistic models will be applied to each subgroup during subgroup analysis.

There will be no interim analyses in this trial.

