### Secondary outcomes and exploratory endpoints

The functional outcome will be evaluated by the modified Rankin scale (mRS) at discharge and 3 months after discharge via outpatient appointment.The cognitive outcome will be evaluated using the Montreal Cognitive Assessment (MoCA) at discharge and 3 months after discharge via outpatient appointment.Adverse events (AEs), including in-hospital pneumonia, intracranial infection, deep vein thrombosis (DVT), and stress ulcer bleeding.Mortality at discharge and 3 months after discharge.Radiographic score, including subarachnoid hemorrhage early brain edema (SEBES) score, modified Fisher scale (mFS) grade, Graeb score.Inflammation parameters, including white blood cell (WBC), neutrophil (NEUT), C-reactive protein (CRP), procalcitonin (PCT), IL-2, IL-6, IL-8, IL-10, TNF-α.Average blood flow velocities (BFVs) of anterior, posterior, and middle cerebral arteries.Levels of vascular endothelial growth factor (VEGF) and endothelin-1 (ET-1).

The detailed schedule of study assessments is shown in Table 1.

**Table 1 Tab1:** Schedule of enrollment, interventions, and assessments

Variables	Visit 1	Visit 2	Visit 3	Visit 4	Visit 5	Visit 6	Visit 7	Visit 8	Visit 8	Visit 9
	Admission within 72 h	Day 1 in ICU	Day 2 in ICU	Day 3 in ICU	Day 4 in ICU	Day 5 in ICU	Day 6 in ICU	Day 7 in ICU	Discharge	90 days
Participants										
Eligibility screen	×									
Informed consent	×									
Randomization		×								
Demographic data	×									
Interventions										
Surgical clipping or endovascular treatment	×									
Inhalation		×								
Assessments										
Modified Rankin scale	×								×	×
GCS	×	×	×	×	×	×	×	×	×	×
WFNS	×									
Hunt and Hess	×									
Modified Fisher	×									
Vital signs	×	×	×	×	×	×	×	×		
Inflammation parameters	×	×		×		×		×	×	×
VEGF	×	×		×		×		×	×	×
ET-1	×	×		×		×		×	×	×
Head CT	×	×						×	×	×
Head CTA + CTP	×								×	×
TCD				×			×			
MoCA									×	×
Adverse events		×	×	×	×	×	×	×	×	×
Detailed ICU therapy								×		
Inhalation time		×	×	×	×	×	×	×		
Inhalation volume		×	×	×	×	×	×	×		

*GCS* Glasgow Coma Scale, *WFNS* World Federation of Neurological Societies, *VEGF* vascular endothelial growth factor, *ET-1* endothelin-1, *TCD* transcranial Doppler

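### The two-group test stated for continuous variables makes no use of the admission value or the repeated sampling of 11 blood markers; a baseline-adjusted longitudinal model would be more precise and give fewer comparisons

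*Protocol article*

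**What the plan says.** All references are to the protocol article.

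- **Markers.** Secondary outcomes and exploratory endpoints lists "Inflammation parameters, including white blood cell (WBC), neutrophil (NEUT), C-reactive protein (CRP), procalcitonin (PCT), IL-2, IL-6, IL-8, IL-10, TNF-α" and, separately, "Levels of vascular endothelial growth factor (VEGF) and endothelin-1 (ET-1").
- **Timing.** Table 1 shows the same seven crosses for the inflammation parameters, VEGF and ET-1: admission, ICU Days 1, 3, 5 and 7, discharge and 90 days. Randomization and the start of inhalation are both marked on ICU Day 1, so the admission sample is a pre-randomization baseline.
- **Test for continuous variables.** Statistical analysis states "Continuous variables will be assessed using either the independent" t-test if the distribution is normal, or otherwise the Mann–Whitney U test.
- **Regression.** The same section adds: "To mitigate preoperative confounding factors, a multiple regression analysis will be employed to compare outcomes between the two groups". It continues: "The results will be reported as adjusted odds ratios (OR) accompanied by 95% confidence intervals (CI"), with values below 1 favouring the experimental arm.
- **Threshold.** "Statistical significance will be defined as a threshold of" P < 0.05, stated once for the whole analysis.

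**The concern.** A two-sample t-test or Mann–Whitney test compares one number per patient between arms. It has no place for a baseline covariate and none for repeated measurements. These markers come with a pre-randomization value and up to six later values per patient, so the stated method suits their structure badly. The regression does not repair this: an odds ratio is not the effect measure for a cytokine concentration, and the sentence mentions neither the admission marker value nor repeated measurement.

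Two things are at stake. Precision that the admission sample could provide is not used. And if each visit is compared separately at 0.05, some isolated significant marker-by-visit results are expected by chance. The Background builds the rationale partly on inflammation, endothelin-1, IL-6 and TNF-α, so such a result could easily be read as support for the mechanism.

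**Working it through.** The article gives no figure for the marker analyses, so there is none to reproduce. The 103 per arm comes from Sample size estimates, concerns DCI and CVS, and serves below only as a scale.

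**1. Number of comparisons**
- Markers: 9 inflammation parameters + VEGF + ET-1 = 11.
- Times: 7 crosses − 1 admission = 6.
- Raw level tested at each later visit: 11 × 6 = 66.
- If the Day 1 sample is drawn before the first inhalation, it cannot show a treatment effect: 11 × 5 = 55.
- MoCA and blood flow velocities are not counted. Table 1 shows no admission assessment for MoCA or TCD.

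**2. False positives under no effect, each test at 0.05**

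| Comparisons m | Expected, 0.05 × m | At least one, 1 − 0.95^m |
|---|---|---|
| 66 | 3.3 | 96.6% |
| 55 | 2.75 | 94.0% |
| 11 (one per marker) | 0.55 | 43.1% |

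The expected number does not require independent tests, because expectations add whatever the correlation. The last column does assume independence. Markers and visits are correlated, so it is an upper guide only.

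**3. Precision from the admission value**

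Let ρ be the correlation between the admission value and the outcome analysed (one visit, or the average over visits). Adjustment multiplies the residual variance by 1 − ρ², so the reduction is ρ². The documents give no ρ; the values below are assumptions.

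| Assumed ρ | Variance factor 1 − ρ² | Reduction | Equivalent n per arm, 103 / (1 − ρ²) |
|---|---|---|---|
| 0.3 | 0.91 | 9% | 113 |
| 0.5 | 0.75 | 25% | 137 |
| 0.7 | 0.51 | 49% | 202 |

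**4. If the test were applied to change from admission**

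That would fit the article's sentence and would use the baseline. With equal variances at both times, the variance factor of a change is 2(1 − ρ): 1.4, 1.0 and 0.6 for ρ = 0.3, 0.5 and 0.7. Against 0.91, 0.75 and 0.51 for adjustment, the change score is less precise in all three cases. At ρ = 0.3 it is worse than ignoring the baseline.

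**The case against.** **The 66 tests are inferred.** The article has one general sentence on continuous variables. It does not mention the markers, does not say that each visit is tested, and does not say whether the variable is a level, a change, a peak or an area under the curve. This stands, so the counts of 66 and 55 are conditional. A reader might infer that the plan prescribes 66 tests; the text does not say so.

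**This is detail for a SAP.** The source is a condensed article, and a SAP may exist. A missing model specification or multiplicity rule would indeed be no finding. The point is narrower: the article does state a method for these variables, and that method is poorly suited to serial data with a baseline.

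**The regression may cover continuous outcomes.** The sentence is not restricted to binary outcomes, and the odds-ratio sentence could be read as describing only those. So an adjusted marker analysis is not ruled out. But the only reported scale does not fit a marker, and its declared target is preoperative confounding.

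**The precision gain is assumed.** This stands. Table 1 places the aneurysm procedure in the admission column. If the admission blood is drawn before the procedure, its correlation with later values, especially at 90 days, may fall below the range shown, and the gain may be small. One ρ for 11 markers and six times is a simplification.

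**The importance is limited.** A reader might infer that the marker results would be biased or invalid, that the primary analysis is affected, or that these markers formally carry a mechanistic claim. The documents support none of these. Randomization keeps each unadjusted comparison valid. The primary outcomes are in-hospital DCI and CVS, which this point does not touch. The mechanism statements in Strengths and limitations and in the Discussion are general and name none of these markers.

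**Conclusion.** The concern holds in a limited form. For continuous variables the article states only an unadjusted two-group test, and its regression is on a scale that does not fit a marker level, although all 11 blood markers have a pre-randomization value and six later ones. Used on raw levels at each visit, the method would leave the admission value unused and produce up to 66 tests with about 3.3 expected false positives, or 55 and 2.75 if the Day 1 sample precedes inhalation.

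The cost is lost precision and weaker error control for secondary or exploratory outcomes. The size of the precision loss rests on an assumed correlation: 9% to 49% of the variance for ρ from 0.3 to 0.7, and less if the correlation is weaker. This is a worthwhile improvement, not a threat to the trial's main conclusion.

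**What to change.** For the blood markers, replace the two-group test, and the choice between t-test and Mann–Whitney by normality, with the following:

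- One repeated-measures model per marker, on the log scale if skewed, containing the admission value, WFNS grade (the factor used in the allocation), time, arm and arm × time.
- As the main result per marker, one average on-treatment effect with its 95% CI over the samples taken after inhalation has started, with patients analysed as allocated. State whether the Day 1 sample is drawn before or after the first inhalation, and include it in the average only if after.
- Discharge and 90-day contrasts from the same model, as descriptive estimates with CIs, so that those samples are not dropped.
- The marker family labelled exploratory. The 11 main comparisons still carry 0.55 expected false positives at 0.05, so the label is needed.
- The odds-ratio sentence restricted to the outcomes it fits.

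The cost is analysis wording and some programming. No extra samples, visits or patients are needed.

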### Randomization

Patients will undergo randomization performed by an intensive critical care (ICU) physician. Allocation will follow a 1:1 ratio through a stratified randomization approach. Allocation will be determined utilizing a minimization method of dynamic allocation, taking into consideration the preprocedural World Federation of Neurological Societies (WFNS) grade as a decisive factor.

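### Allocation is balanced on WFNS grade, but the named tests for DCI and CVS ignore it, and the plan does not say whether those tests or the regression decide

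*Protocol article*

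**What the plan says.** **Allocation.** The Randomization section states: "Allocation will follow a 1:1 ratio through a stratified randomization approach". It then describes dynamic allocation by minimization, "taking into consideration the preprocedural World Federation of Neurological Societies (WFNS) grade as a decisive factor". Whether the scheme is called stratified or minimized, its purpose is to balance the arms on WFNS.

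**Tests.** The Sample size estimates section states: "The primary study outcomes encompass the incidence of in-hospital DCI and CVS". Both outcomes are yes/no, so they fall under this sentence of the Statistical analysis section: "Dichotomized variables will be compared utilizing the Pearson chi-square test", with Fisher's test as the alternative.

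**Regression.** The same section continues: "To mitigate preoperative confounding factors, a multiple regression analysis will be employed to compare outcomes between the two groups". Results are then to be given as adjusted odds ratios with 95% confidence intervals. The covariates are not listed.

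**WFNS in the analysis text.** It appears once, in the list of subgroups: "Subgroups analysis will be performed, including subgroup by age, sex, WFNS, mFS, and treatment modality".

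**Decision rule.** Significance is set at P < 0.05. No sentence says whether the chi-square/Fisher test or the regression is the analysis to which that threshold applies for DCI and CVS.

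**The concern.** Balancing the arms on a prognostic factor removes that factor's contribution to the chance difference between arms. A chi-square or Fisher test does not know this. It computes its standard error as if WFNS could still be imbalanced by chance, so the standard error is too large whenever WFNS predicts the outcome. The test then rejects a true null less often than 5% of the time and loses some power. A model that contains WFNS matches its standard error to the design.

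The second issue is the lack of ranking. Two analyses of the same primary outcomes stand side by side, and they can fall on opposite sides of P = 0.05. Other parts of the article point in different directions: the sample size was derived from two bare proportions, while the reporting sentence promises adjusted odds ratios. The stated reason for the regression, confounding, also does not settle the matter. In a randomized trial, the reasons to adjust are to reflect the allocation scheme and to gain precision, and both point first to WFNS.

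**Working it through.** **1. Which test the sample size fits.** Inputs from Sample size estimates: 45% control, 23% experimental, alpha 0.05, power 90%, 103 per arm. Sidedness is not stated; two-sided is assumed.

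Pooled two-proportion formula, with mean proportion 0.34 and difference 0.22:

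n = [1.96·√(2·0.34·0.66) + 1.2816·√(0.45·0.55 + 0.23·0.77)]² / 0.22² = (1.313 + 0.835)² / 0.0484 ≈ 95.3, so 96 per arm.

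With continuity correction: n′ = (95.3/4)·[1 + √(1 + 4/(95.3·0.22))]² ≈ 104.2, so 105 per arm, within 2 patients of the stated 103. At 103 per arm, exact power is 89.9% for Fisher's test and 92.2% for the uncorrected chi-square. So 103 is consistent with an unadjusted Fisher or continuity-corrected comparison. The section describes no covariate input.

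**2. Effect of ignoring WFNS.** The article gives neither the WFNS distribution nor its association with DCI or CVS, so both are assumed. Simulation settings: 206 patients; grades I–V at 40/22/8/15/15%; minimization on WFNS alone, with probability 0.85 of assigning the arm that reduces imbalance; 4,000 trials per setting; odds ratio per grade varied from 1.0 (no association) to 2.7. The uncorrected chi-square test is compared with a logistic regression on treatment and WFNS grade (categorical). Simulation error is about √(0.05·0.95/4000) ≈ 0.35 points at 5%.

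| Assumed OR per grade | 1.0 | 1.35 | 1.65 | 2.0 | 2.7 |
|---|---|---|---|---|---|
| Type I error, chi-square (45% in both arms) | 4.7% | 4.8% | 3.9% | 2.9% | 1.6% |
| Type I error, with WFNS | 4.9% | 5.5% | 5.4% | 5.2% | 4.8% |
| Power, chi-square (45% vs 23%) | 92.9% | 92.9% | 93.1% | 95.0% | 96.3% |
| Power, with WFNS | 92.9% | 93.6% | 94.8% | 97.2% | 98.7% |

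With 34% in both arms the pattern is the same: at ORs of 1.65 / 2.0 / 2.7, chi-square type I error is 3.8 / 2.7 / 1.1%, against 5.1 / 5.0 / 4.6% with WFNS.

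**3. Check through the standard error.** Under the 45% null, compare the mean unadjusted standard error of the risk difference with its true standard deviation across simulated trials. If the standard error is too large by a factor r, the real type I error is 2Φ(−1.96·r).

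- OR 1.0: r = 0.06899/0.06869 = 1.004, giving 4.9%
- OR 1.35: r = 0.06900/0.06795 = 1.015, giving 4.7%
- OR 1.65: r = 0.06901/0.06546 = 1.054, giving 3.9%
- OR 2.0: r = 0.06901/0.06196 = 1.114, giving 2.9%
- OR 2.7: r = 0.06906/0.05601 = 1.233, giving 1.6%

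These agree with the simulated rejection rates within simulation error, so the overstated standard error accounts for the conservatism.

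**The case against.** **The regression may already do the right thing.** WFNS is described as preprocedural and the regression adjusts for preoperative factors, so WFNS fits its wording and may well be included. A full covariate list is properly left to an analysis plan, which is not shown. This stands: the absence of a list is not the point. What remains is that the article itself sets two analyses side by side for the same outcomes without ranking them, and the one it names most concretely ignores the allocation factor.

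**The reported intervals need not be wrong.** A reader might infer that the trial will publish wrong error bars. The article does not support this. The only intervals it promises belong to the adjusted odds ratios, and those are sound if WFNS is in the model. The excess width affects the unadjusted comparison only.

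**The error is on the safe side.** A reader might also infer that false positives are inflated. The reverse is true of the unadjusted test. At an odds ratio of 1.35 per grade or below, the departure from 5% is within simulation error.

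**Little power is at stake at the planned effect.** This stands too: simulated chi-square power is 92.9% or more throughout.

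**Free choice of the better result.** It is tempting to say that the sponsor may report whichever analysis looks better. The adjusted-odds-ratio sentence leans towards the regression as the headline, so that claim goes too far. The sentence governs how results are reported, however, and does not say which P value decides.

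**Conclusion.** The point holds in a limited form. Allocation is balanced on WFNS, the named tests for DCI and CVS ignore WFNS, the regression is not tied to it, and no deciding analysis is named.

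The cost is conditional. If the unadjusted test decides and WFNS predicts outcome with an odds ratio of 1.65 to 2.0 per grade, the real type I error is about 3 to 4% instead of 5%, and the standard error of the risk difference is about 5 to 11% too large. Across the whole assumed range, the power loss at 45% versus 23% is 0 to 2.5 points, and chi-square power stays above the planned 90%. If WFNS is only weakly related to outcome, the loss is negligible. If the regression decides and contains WFNS, there is none. These figures rest on the assumed grade mix, association and allocation probability, none of which the article gives.

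Severity is minor to moderate. It is an improvement available at no cost, and does not invalidate the trial.

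**What to change.** State in the Statistical analysis section that the primary analysis of DCI, and separately of CVS, is a logistic regression of all randomized patients on treatment and WFNS grade. Its P value decides, and it is reported as the adjusted odds ratio with 95% confidence interval. Label the chi-square and Fisher comparisons as supportive. Give the reason for the WFNS term as the allocation scheme and precision, not confounding.

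The cost is a few sentences. WFNS is already recorded at the first visit, and adjusted odds ratios are already promised. The 103 per arm, sized for an unadjusted test, does not need to change. The wording should be settled before outcome data are compared by arm.
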